## Abstract

Introduction: Irritable bowel syndrome (IBS) symptoms can be effectively managed with the low FODMAP diet. However, its efficacy in reducing inflammation is not yet proven. On the contrary, the Mediterranean diet has anti-inflammatory properties with proven efficacy in treating chronic low-grade inflammation-related diseases. Aim: To publicly share our protocol evaluating the efficacy of the Mediterranean low-FODMAP (MED-LFD) versus NICE recommendations (British National Institute for Health and Care Excellence) diet in managing IBS symptoms and quality of life. Materials and Methods: Participants meeting the Rome IV criteria will be randomly assigned to MED-LFD or NICE recommendations and they will be followed for six months. Efficacy, symptom relief, quality of life and mental health will be assessed using validated questionnaires. In addition, fecal samples will be analyzed to assess gut microbiota, and to measure branched and short-chain fatty acids, and volatile organic compounds (metabolic byproducts from bacteria). Expected results and discussion: By publicly sharing this clinical study protocol, we aim to improve research quality in the field of IBS management by allowing for peer review feedback, preventing data manipulation, reducing redundant research efforts, mitigating publication bias, and empowering patient decision-making. We expect that this protocol will show that MED-LFD can effectively alleviate IBS symptoms and it will provide pathophysiology insights on its efficacy. The new dietary pattern that combines the LFD and the MED approaches allows for the observation of the synergistic action of both diets, with the MED’s anti-inflammatory and prebiotic properties enhancing the effects of the LFD while minimizing its limitations. Identifier in Clinical Trials: NCT03997708

## 1. Introduction

The Rome IV criteria highlighted a new insight into IBS’s pathophysiology, giving importance to the gut-brain axis interactions and to the low-grade inflammation restricted to the gut mucosa [1,2]. This low-grade mucosal inflammation, represented by the presence of mucosal enteroendocrine cells and T lymphocytes detected in rectal mucosa biopsy specimens and visceral hypersensitivity are present in all IBS subtypes, providing evidence that IBS has a structural component [3]. Research on the gut microbiota through a mega-cohort analysis revealed significantly lower α-diversity in IBS participants’ feces than in healthy controls, confirming that gut bacterial dysbiosis is associated with the above syndrome [4]. In a newly published review, gut microbiota in these patients showed reductions in *Bifidobacterium*, *Lactobacillus*, and *Faecalibacterium prausnitzii* relative abundances, increased levels of Firmicutes, and decreased *Bacteroidetes* (with an increased ratio of *Firmicutes*: *Bacteroidetes* ratio) at the phylum level [5]. *Lactobacillus* spp. and *Bifidobacterium* spp. are commensal bacteria that have probiotic properties and contribute to gut health [6]. Multiple meta-analyses have shown that probiotics have a positive effect on the symptoms of gastrointestinal ailments, including IBS [7], while *F. prausnitzii*, has anti-inflammatory functions that can also contribute to overall gut health [8]. They also identified several changes at lower taxonomic levels, including increased concentrations of *Clostridia* and *Clostridiales* [5]. *Clostridia* strains promote the release of IL-10, a protein that helps regulate the immune system. Seventeen bacterial strains from a healthy human fecal sample belonging to the *Clostridium* clusters IV, XIVa, and XVIII have been found to increase the number and function of colonic regulatory T cells in rodents. This is important because the *Clostridium* class is known to colonize the area around the colon’s mucosa, and it includes several major butyrate producers. These bacteria likely play a crucial role in regulating the host’s immune system. Additionally, some species within the *Clostridia* class are capable of producing biologically active catecholamines, such as norepinephrine and dopamine, which are neurotransmitters. This has been demonstrated in experiments with gnotobiotic and germ-free mice. Therefore, *Clostridia* seems to be particularly involved in the pathophysiology of IBS because of its important role not only in gastrointestinal immune homeostasis but also in the gut-brain axis [9]. On the other hand, the review detected decreased concentrations of *Bacteroidia* and *Bacteroidales*, while *Escherichia coli* and *Enterobacter* were found to increase in patients with gastrointestinal ailments compared to healthy controls [5]. *Bacteroides* are Gram-negative bacteria that help the host to obtain nutrients by breaking down food. However, in an unhealthy gastrointestinal environment, they can cause various endogenous infections and intraabdominal abscesses. Recently, they have also been associated with colon cancer. *Enterobacteriaceae* contain molecular components that directly enhance the inflammatory response, making them potentially harmful to gut health [10]. Environmental factors, like diet, are dominating in shaping the architecture of gut bacteria. Furthermore, up to 89% of IBS participants associate their symptoms with specific food consumption and 90% of them choose to eat less to reduce postprandial discomfort [3].

The low-FODMAP diet (LFD) is a well-documented intervention that reduces the symptoms of IBS and may represent the first-line treatment. The core mechanism of Fermentable oligo-, di-, monosaccharides, and polyols (FODMAPs) is related to their ability to attract water, which increases the volume of the fluid in the gut and contributes to its osmotic activity. Moreover, they provide food for bacterial populations, which ferment and produce gas [11].

On the other hand, the Mediterranean diet (MED) is mainly based on plant foods, with fish and poultry being the primary sources of animal products and a limited amount of dairy. Olive oil, being a significant product of the Mediterranean region, is also an essential component of this diet [12]. MED has antioxidant and anti-inflammatory properties that promote gut health through high amounts of phenolic compounds. Additionally, MED has been associated with an increased abundance of short-chain fatty acids (SCFAs) that help maintain a functional intestinal epithelium. Furthermore, olive oil, the primary source of fats in MED, has been linked to decreased intestinal inflammation and visceral hypersensitivity in animal studies. However, until recently, few studies have explored the impact of the MED on IBS symptoms [13,14]. In a recent study, a higher adherence to MED was associated with a lower abundance of potentially harmful *Faecalitalea, Streptococcus*, and *Intestinibacter*, and a higher abundance of potentially beneficial *Holdemanella* from the *Firmicutes* phylum [13].

In parallel, the nutritional recommendations of the British National Institute for Health and Care Excellence (NICE) for managing IBS represent some of the most commonly used guidance in clinical practice, based on dietary and lifestyle modifications [15].

Taking into consideration that LFD reduces IBS symptoms, but its efficacy regarding the reduction in inflammation is not proven, and that the MED is effective for chronic low-grade inflammation-related diseases, we are trying to determine the LFD’s benefits combined with the Mediterranean diets’ anti-inflammatory properties [15]. We aim to design and publicly share a randomized, open-labelled, placebo-controlled trial to evaluate the efficacy of the Mediterranean-LFD (MED-LFD) in comparison with the nutritional recommendations of the British National Institute for Health and Care Excellence for managing IBS symptoms.

## 2. Materials and Methods

### 2.1. Eligibility Criteria

Patients 18–65 years of age living in Greece who present with IBS symptoms will be assessed for fulfillment of the Rome IV diagnostic criteria for IBS diagnosis. Patients with Bristol Stool Form Scale (BSFS) types 3–7 with moderate to severe symptoms measured with IBS severity scoring system (IBS-SSS) > 175 will be enrolled. Full blood count, C reactive protein (CRP) or erythrocyte sedimentation rate (ESR), serum thyroid-stimulating hormone (TSH) within normal levels, negative results for tissue transglutaminase (tTg), immunoglobulin A or G antibodies (IgA or IgG) and negative fecal calprotectin are prerequisites for eligibility in the study. Participants > 50 years old should have completed colorectal cancer screening before enrollment.

### 2.2. Exclusion Criteria

Presence of (a) red flag symptoms, signs and/or laboratory findings indicating organic gastrointestinal disease like anemia, nocturnal diarrhea, gastrointestinal bleeding, unexplained weight loss, initiation of bowel symptoms after the age of 50, anorexia, systemic symptoms of inflammation like fever, persistent or deteriorating diarrhea and/or pain, fatigue, abnormal full blood count (FBC), high ESR or high CRP, (b) systemic disease requiring specialized diet, like cardiovascular disease, chronic renal failure, chronic liver disease or diabetes mellitus, celiac disease, cerebrovascular disease, major abdominal surgery, inflammatory bowel disease, (c) pregnancy, (d) breastfeeding, (e) IBS–constipation subtype (BSFS 1–2), (f) probiotic and antibiotic treatment within 1 month of day 1, (g) current hypnotherapy or cognitive behavior therapy, (h) history of food allergies, (i) inability to stop antispasmodic and/or antidiarrheal medications throughout the study period, (j) inability to follow the study requirements. Participants with an IBS-SSS score equal to or less than 175 will be also excluded.

### 2.3. Bioethics

The study will be conducted according to the Declaration of Helsinki following approval by the Institutional Ethics Committee of the University General Hospital “ATTIKON” (EBΔ435/19-06-2018). Written informed consent will be obtained from each participant following a detailed explanation of the objectives and protocol of the study.

This randomized clinical trial is registered under ClinicalTrials.gov, https://clinicaltrials.gov/ (accessed on 15 April 2024); Identifier: NCT03997708.

### 2.4. Interventions

MED-LFD and NICE diets will be provided to all participants by experienced dieticians in delivering LFD, following an initial consultation expected to last approximately 30 min.

#### 2.4.1. Randomization

We have prepared a random allocation sequence using block randomization, with a 1:1 ratio of control to intervention group (block size *n* = 4). Participants will be informed that both diets may reduce their symptoms but diet masking is impossible.

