### 2.11. Statistics

#### 2.11.1. Sample Size Calculation

The sample size was calculated at 108 participants (54 per group) with expected values taken from the meta-analysis of Varju et al. [38] and a pre-specified statistical power of 80%, significance level α = 0.05, and 10% adjustment for non-adherence to detect a significant improvement in the primary outcome measure 100 vs. 59 points (estimated standard deviation = 60) in the MED-LFD and NICE groups, respectively.

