## 3. Expected Results and Discussion

During the last two decades, campaigns initiated by impact journals have advocated for access to original trial data, including the case record forms [41]. Sharing clinical study protocols can significantly enhance the caliber of research through various means: It permits researchers to receive input on their protocols via peer review, although studies with ethical approval or funding often receive feedback on initial drafts. However, even the most meticulously planned study might encounter challenges defending contentious elements in its protocol. Moreover, the publication of protocols facilitates comparisons between the original intentions and the actual execution, crucial for preventing data manipulation or selective reporting. Making study protocols public helps researchers comprehend ongoing studies, curbing redundant research efforts. It also assists systematic reviewers in identifying trials, potentially mitigating publication bias. Lastly, the disclosure of study protocols allows participants to identify studies they might consider participating in, empowering their decision-making process [42].

We present herein our single-center, randomized controlled study to evaluate the clinical effects of the LFD combined with the elements of the MΕD in comparison to the dietetic consultations of the NICE for the management of IBS symptoms. Additionally, we foresee the conduction of two physiology studies aiming to better understand the clinical results of the study.

Chen et al. found that while standard MΕD was not associated with the severity of the disease, certain MED foods were linked to symptoms indicating personalized management for those with severe symptoms [13]. Paduano et al. concluded that MΕD is well-accepted and easier to follow than other proposed diets for short-term periods (4 weeks), while they did not find evidence of LFD superiority against MED in improving the quality of life of IBS participants [14]. Moreover, a diet that excludes nutrient-rich foods can lead to nutritional inadequacy. Introducing LFD for a long period can result in insufficient intake of essential nutrients like carbohydrates, fiber, iron, folate, magnesium, vitamin C, B vitamins, and calcium [43,44,45].

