Our study protocol has limitations. One of these is the lack of blinding; this will affect the clinical response to some extent. Additionally, we are unable to examine the effects of systematically altering dietary fiber intake in IBS patients because we do not differentiate between soluble and insoluble dietary fibers. A serious limitation for a trial that wishes to prove the advantages of a Mediterranean pattern compared to the comparator is that both groups will have similar access to extra virgin olive oil intake—the primary source of fat in Greek cuisine—and its anti-inflammatory properties benefitting the entire IBS cohort [51]. Another limitation is that some methodologies appear resource-intensive, involving sophisticated equipment and specialized reagents (e.g., Nanopore, GC/MS). Although such resource requirements could pose challenges for replication and broader implementation in settings with limited access to these resources, these are referred to as exploratory analyses to understand more clearly the pathophysiology dietary manipulation on microbiota and on BCFAs/SCFAs production in IBS. While potential changes in gut microbiota composition may be notable, a critical assessment requires considering various factors such as study design, context, causality, functional implications, and the complexity of the gut microbial ecosystem. Further research and a nuanced approach might be necessary to draw meaningful conclusions about the implications of these microbiota changes in different health conditions.

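### A single published block size of 4 in an open-label, single-centre trial could let enrolling staff who follow earlier allocations deduce one allocation in three

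*Protocol article*

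**What the plan says.** Section 2.4.1 of the protocol article reports that the allocation sequence already exists and was made by "block randomization, with a 1:1 ratio of control to intervention group (block size *n* = 4". One block size is given; neither varying sizes nor stratification factors are mentioned. The same section says that "diet masking is impossible", and the Introduction calls the study a "randomized, open-labelled, placebo-controlled trial", of which only the open-label part matters here. Section 3 describes it as "our single-center, randomized controlled study". Section 2.11.1 gives the number to be randomised: "The sample size was calculated at 108 participants (54 per group" in each arm, as planned.

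Section 3 names the open design as a limitation: "One of these is the lack of blinding; this will affect the clinical response to some extent". That sentence concerns how patients respond. It does not consider what open allocation, combined with a small fixed block, may reveal at enrolment.

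**The concern.** Blocking keeps the arms balanced by forcing each run of four patients to contain two of each diet. Once either diet has been used twice in a block, the remaining places are determined. In a masked trial this is harmless, because nobody at the site sees which treatments have been given. Here each past allocation is visible, there is one site and apparently one list, and the block size is in print. The history needed for the deduction could therefore be available to whoever decides on the next patient.

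Foreknowledge matters only if it can influence who is entered or when. Section 2.2 leaves some room for that, since one exclusion rests on a judgement that the patient could not comply with the study and others depend on how symptoms are interpreted. The main outcomes (IBS-SSS, adequate relief, quality of life, HADS) are self-reported, so a difference between arms in motivation or expectation could pass into the treatment comparison.

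**Working it through.** The article gives no predictability figure, so there is none to reproduce. The calculation is an exact enumeration.

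**Inputs**
- Block size 4, ratio 1:1, so two of each diet per block (section 2.4.1).
- Past allocations visible (section 2.4.1; open label in the Introduction).
- One centre (section 3).
- 108 participants, so 108/4 = 27 complete blocks (section 2.11.1).
- Assumption, not stated in the article: the person enrolling knows the block size and sees the earlier allocations in order.

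**Fixed block of 4.** There are C(4,2) = 6 equally likely blocks. By position within the block:

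| Position | Probability that it is certain | Probability that the best guess is right |
|---|---|---|
| 1 | 0 | 1/2 |
| 2 | 0 | 2/3 |
| 3 | 1/3 (first two alike: 2 of 6 blocks) | 1/3 × 1 + 2/3 × 1/2 = 2/3 |
| 4 | 1 | 1 |

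- Share certain in advance: (0 + 0 + 1/3 + 1)/4 = 1/3 = 33.3%. Over the trial: 108 × 1/3 = 36.
- Share guessed correctly by always naming the arm that is behind: (1/2 + 2/3 + 2/3 + 1)/4 = 17/24 = 70.8%. Over the trial: 108 × 17/24 = 76.5, against 54 by chance.

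If undisclosed strata existed, the one-third rate would still hold within each complete block.

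**Alternatives.** Fixed blocks of 6 and 8 were enumerated in the same way. Randomly varied blocks were simulated (2,000 trials of 108), with sizes equally likely and an observer who knows the set of possible sizes and the full history.

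| Scheme | Certain in advance | Of 108 | Best guess correct |
|---|---|---|---|
| Fixed 4 (plan) | 33.3% | 36 | 70.8% |
| Fixed 6 | 25.0% | 27 | 68.3% |
| Fixed 8 | 20.0% | 21.6 | 66.6% |
| Varied 4, 6 | 5.5% | about 6 | 69.2% |
| Varied 4, 6, 8 | 2.3% | 2 to 3 | 67.9% |

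Varying the size removes most of the certainty because the observer no longer knows where a block ends. It removes little of the guessing advantage, because the arm that is behind remains the more likely one under any scheme that forces balance.

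**The case against.** A fixed block of 4 is a valid way to randomise 1:1, 108 divides into complete blocks, and nothing in the article contradicts it. The deduction needs two conditions, and the article establishes neither for the people who enrol. It does not say who recruits, and the staff it places with allocated participants are the dieticians, who are not said to judge eligibility. Who holds the list and how it is concealed are matters that an article commonly leaves to the full protocol, so that silence is not a fault. Most eligibility items can be checked objectively (age, Rome IV, laboratory tests, stool type), and the requirement of IBS-SSS above 175 limits how mild an enrolled patient can be. The figures above measure predictability; they do not measure bias in IBS-SSS or in responder rates.

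All of this stands, and it limits the point. Three stronger readings are tempting but not supported:
- *That recruiting staff will know one allocation in three.* This is conditional on knowing the block size and following the history.
- *That no form of concealment could prevent it.* Hiding the next entry alone would not, but keeping enrolling staff unaware of the block size or of past allocations would, and nothing shown rules that out. Publication weakens only the first of these protections.
- *That the analysis could do nothing about the result.* Baseline IBS-SSS is measured, so an imbalance in severity could be seen and partly adjusted for. Unmeasured differences could not; motivation is not among the baseline data listed in section 2.8.

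What remains is that the block size is a stated choice, it is public, and the design makes past allocations visible.

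**Conclusion.** The point holds as a conditional weakness in a stated design choice. If enrolling staff know the block size and follow earlier allocations, about 36 of 108 allocations are certain in advance and 71% can be guessed correctly. Those figures are exact for complete 1:1 blocks of 4. The document shows an opportunity for selection bias; it does not show that anyone used it, and it gives no basis for putting a size on any resulting bias in the treatment effect. The change is a cheap improvement, and nothing here makes the planned randomisation invalid.

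**What to change.** Generate the sequence with randomly varying block sizes, for example 4, 6 and 8, and do not disclose the sizes to enrolling staff. If enrolment has begun, do this for the unused remainder, starting where a block of 4 has been completed. Section 2.4.1 should then say that block sizes vary at random, without listing them.

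The gain is in certainty: from 33% of allocations to about 2% (2 to 3 of 108), even if staff learn the set of sizes. Best-guess accuracy falls only from 71% to about 68%, so the change reduces the problem without removing it.

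The cost is that a list already prepared has to be replaced and the change recorded. The final imbalance could reach 4 participants if the trial stops halfway through a block of 8 (8/2 = 4), against none when 27 blocks of 4 are completed. With 54 planned per arm that is small. The article does not state enrolment status, so how much of the list can still be replaced is unknown.

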#### 2.4.2. Control Group

Participants in the control group will receive a weekly dietary plan for four weeks according to NICE guidelines for IBS participants [16], in which they may choose with free will foods from specific categories, i.e., vegetables, fruits, and grains. This includes regular meals, avoiding eating too little or too much, staying hydrated, reducing the intake of caffeine, alcohol, fizzy drinks, fatty, spicy, and processed foods, limiting fresh fruit intake to a maximum of three servings per day (approximately 80 g), high-fiber food (such as whole meal or high-fiber flour and bread, cereals high in bran, and whole grains such as brown rice), resistant starch, and sweeteners, and addressing any perceived food intolerances such as dairy [16]. An indicative analysis of the mean daily nutrition information of the NICE diet recommendation per week using https://explorefood.foodafactoflife.org.uk (accessed on 10 January 2024), is presented in Table 1.

#### 2.4.3. The MED-LFD Group

MED-LFD group (intervention) will receive a weekly dietary plan in line with their energy needs, adapted to the first phase (restrictive phase) of the strict LFD: the FODMAP content will not exceed 0.77–1.91 g per day (according to Monash University labs measurements, accessed on 21 October 2019). In this weekly plan, there is a free choice of animal protein, but participants will be strongly advised to consume fish 2–3 times/week and to reduce red meat to once per week. Furthermore, they will be guided to eat vegetables in small quantities, low in FODMADs, and to drink wine optionally, in the context of the Mediterranean way of life [17]. The components of the MED combined with LFD, acting synergistically without changing the initial profile of LFD, have been published in detail elsewhere [3]. An indicative analysis of the mean daily nutrition information of the restrictive phase of MED-LFD per week using https://explorefood.foodafactoflife.org.uk (accessed on 10 January 2024), is presented in Table 1.

